## Abstract

**Background:**

French Polynesia is a French overseas collectivity in the Southeast Pacific, comprising 75 inhabited islands across five archipelagoes. The human settlement of the region corresponds to the last massive migration of humans to empty territories, but its timeline is still debated. Despite their recent population history and geographical isolation, inhabitants of French Polynesia experience health issues similar to those of continental countries. Modern lifestyles and increased longevity have led to a rise in non-communicable diseases (NCDs) such as obesity, diabetes, hypertension, and cardiovascular diseases. Likewise, international trade and people mobility have caused the emergence of communicable diseases (CDs) including mosquito-borne and respiratory diseases. Additionally, chronic pathologies including acute rheumatic fever, liver diseases, and ciguatera, are highly prevalent in French Polynesia. However, data on such diseases are scarce and not representative of the geographic fragmentation of the population.

**Objectives:**

The present project aims to estimate the prevalence of several NCDs and CDs in the population of the five archipelagoes, and identify associated risk factors. Moreover, genetic analyses will contribute to determine the sequence and timings of the peopling history of French Polynesia, and identify causal links between past genetic adaptation to island environments, and present-day susceptibility to certain diseases.

**Methods:**

This cross-sectional survey is based on the random selection of 2,100 adults aged 18–69 years and residing on 18 islands from the five archipelagoes. Each participant answered a questionnaire on a wide range of topics (including demographic characteristics, lifestyle habits and medical history), underwent physical measurements (height, weight, waist circumference, arterial pressure, and skin pigmentation), and provided biological samples (blood, saliva, and stool) for biological, genetic and microbiological analyses.

**Conclusion:**

For the first time in French Polynesia, the present project allows to collect a wide range of data to explore the existence of indicators and/or risk factors for multiple pathologies of public health concern. The results will help health authorities to adapt actions and preventive measures aimed at reducing the incidence of NCDs and CDs. Moreover, the new genomic data generated in this study, combined with anthropological data, will increase our understanding of the peopling history of French Polynesia.

**Clinical trial registration:**

https://clinicaltrials.gov/, identifier: NCT06133400.

## Introduction

French Polynesia is located in the Southeast Pacific and within the Polynesian triangle, which is bounded by the islands of Hawaii to the North, Aotearoa (New Zealand) to the West and Rapa Nui (Easter Island) to the East. This French overseas collectivity extends over a maritime area as large as Europe and includes 121 islands, of which 75 are inhabited, distributed within five archipelagoes: Society, Marquesas, Tuamotu, Gambier and Austral (Figure 1). According to the previous national population census conducted in 2017, there are about 276,000 inhabitants distributed in the various archipelagoes, of which nearly 75% are concentrated in the islands of Tahiti and Moorea (Windward Islands, Society archipelago) (1).

**Figure 1 F1:**
[figure not shown]
Map of French Polynesia showing the geographical distribution of the five archipelagoes (Society, Tuamotu, Gambier, Marquesas and Austral) compared to the European continent (showed at the same scale). Flight connections between Tahiti and the islands selected for the survey are indicated by red lines. Inset map at upper left shows location of French Polynesia (red circle) within the Polynesian triangle (black triangle) bounded by the islands of Hawaii, New Zealand and Easter Island in the Pacific Ocean.

In the course of the history of human migrations around the world, Pacific islands, and East Polynesia in particular, were the last empty lands to be settled. This settlement process began approximately 1,200 to 1,000 years ago and ended around 750 years ago (2). Although archaeological and linguistic data have provided evidence for the geographical and temporal origin of the populations of the Eastern Pacific islands, the sequence and timings of settlement of the Polynesian islands are still debated (3). To help elucidate these gaps, a few genetic studies including samples from Pacific populations have been conducted over the past five years (2– 6). However, for the studies involving the use of samples from the population of French Polynesia, only a limited number of samples collected in a few islands were available. Some studies also aimed to identify genomic variations related to adaptation of the populations to island environments. In a study including genomes from 20 populations from the Pacific region, candidate variants for positive selection were found in genes related to immunity and metabolism, suggesting genetic adaptation to pathogens and food sources specific to Pacific islands (4). However, further investigations are needed to identify causal links between past genetic adaptation and present-day disease risk in Pacific settings. Indeed, most studies investigating genetic links with vulnerabilities to non-communicable (NCDs) and communicable (CDs) diseases have focused on populations in Africa, Europe, Asia, and the USA (7–10). The same observation is made for the research investigating the link between human gut microbiome composition and susceptibility to diseases (7). Despite the high burden of various NCDs and CDs, Pacific islands remain highly underrepresented in genomic studies.

In addition to genetic and microbial factors, social and environmental factors such as poverty, education, and access to healthcare are thought to be major drivers of disease burden in the Pacific islands (7). In French Polynesia, prevention measures against NCDs and CDs have been enhanced, and access to healthcare has been improved in all archipelagoes over the past 3 decades (11). This has certainly contributed to the extension of life expectancy at birth, which has increased from 67.1 years to 74.7 for men and 72.8 years to 79.1 for women between 1990 and 2020 (12). However, transition from traditional to modern lifestyles in the Pacific islands (including overconsumption of processed food along with reduced uptake of fruit and vegetables, as well as physical inactivity) and increased longevity have led to a rise in the incidence of NCDs (13). The most recent data collected in French Polynesia in 2010 indicated that the prevalence of obesity and hypertension in adults was 40.4% and 26.7%, respectively. It was estimated that only 1.7% of the population of French Polynesia presented a low risk of developing a NCD whereas 45% were at high risk (14). According to the latest reports from the health authorities of French Polynesia, the leading causes of death are cardiovascular diseases (26.1%) mainly associated with lifestyle, and cancers (25.1%) (15, 16). Among the Pacific island countries and territories (PICTs), French Polynesia displayed one of the highest age-standardized cancer incidence (267.9 for males and 214.0 for females per 100,000) and age-standardized cancer mortality (157.2 for males and 106.8 for females per 100,000) in 2020 (17–19). The most frequently reported cancers are prostate (73.3 per 100,000), breast (66.5 per 100,000), lung (40.4 per 100,000), thyroid (16.1 per 100,000), and colorectal (12.3 per 100,000) cancers (19). Moreover, the incidence of hepatocellular carcinoma recorded in the Austral archipelago between 2013 and 2017 is among the highest in the world (43.1/100,000 inhabitants), this pathology being associated with a high prevalence of infection with hepatitis B virus (HBV) and obesity (20).

Dietary habits, especially high fish consumption, also expose the population of French Polynesia to seafood-related NCDs. Among them, ciguatera poisoning, a disease caused by the consumption of reef fishes or marine invertebrates contaminated by neurotoxins (ciguatoxins) produced by a microalgae that belongs to the *Gambierdiscus* genus, is highly prevalent in French Polynesia where it constitutes an important public health issue (21). In 2021, the overall incidence rate of ciguatera, based on the number of symptomatic cases reported by healthcare workers or by the patients themselves, was 6.9/10,000 inhabitants (22). However, as (i) ciguatera is not on the list of notifiable diseases, (ii) a large proportion of ciguatera-affected people do not consult a healthcare worker, and (iii) cases requiring emergency care or hospitalization in the main hospital of French Polynesia (*Centre Hospitalier de la Polynésie française*, Tahiti) are not systematically recorded, the true incidence rate of this disease is underestimated. Another source of seafood-related contaminants are heavy metals including mercury and lead. Indeed, high levels of mercury were detected in adolescents and adults from two atolls of the Tuamotu archipelago (Hao and Makemo) (23), in adults from the Leeward islands (Tahiti and Moorea) (24), and in cord blood samples of delivering women from all archipelagoes, suggesting that Polynesian newborns may be prenatally exposed to high doses of mercury (25). Moreover, concentrations of lead exceeding toxicological reference values were found in a significant proportion of the residents of Hao and Makemo islands tested to assess their exposure to toxic metals and polychlorinated biphenyls (PCBs) (23). Although levels of PCBs found in both atolls were low compared to international standards, there was a higher body burden of PCBs in residents of Hao which was suggested to be potentially linked to some contamination of the environment by military support activities in this island. Another source of environmental contamination that may have an impact on the population's health are pesticides. To our knowledge, there are no data concerning the level of exposure to pesticides of the population of French Polynesia. However, surveys on the pollution of French Polynesia coral reefs by pesticides found the presence of herbicides and insecticides in fishes which are commonly consumed by the local inhabitants (26–28).

In addition to NCDs, CDs represent major health problems in French Polynesia. As a result of the prevention, screening, treatment and vaccination programs implemented by the health authorities, the incidence of several CDs has decreased (29). Despite these efforts, some CDs caused by bacterial infections persist, including leprosy (mean incidence of 1.6 cases per 100,000 inhabitants reported from 2000 to 2017) and tuberculosis (incidence of 19.4 cases per 100,000 inhabitants in 2018) (30, 31). As a comparison, the last epidemiological survey of leprosy conducted in metropolitan France in 2010 showed a prevalence of 0.011 per 10,000 inhabitants, with most cases imported from French overseas territories (32), and the incidence of tuberculosis reported in metropolitan France in 2021 was 6.4 cases per 100,000 inhabitants (33). Moreover, in 2013, the prevalence of Bancroftian lymphatic filariasis, an infection caused by the nematode worm *Wuchereria bancrofti* transmitted by mosquitoes, had still not reached the elimination threshold (*i.e.,* filarial antigenemia <1%) defined by the World Health Organization (WHO) in Tahiti, Huahine (Leeward Islands, Society archipelago) and three islands in the Marquesas archipelago (Tahuata, Hiva Oa and Fatu Hiva), despite several years of community treatment (34–37). Furthermore, HBV remains a public health problem, despite the availability of an effective vaccine. Following the finding of hepatitis B surface antigens (HBsAg) among 10.48% inhabitants of the Austral archipelago randomly selected in 1987 (38), vaccination of children at birth started to be implemented in 1992 to decrease the burden of chronic HBV infection in French Polynesia (39), and became mandatory in 1995 (40). A nationwide serosurvey conducted in 2014 in 6-year-old schoolchildren from the five archipelagoes showed a three-dose vaccination coverage of 98% and a prevalence of HBsAg of 0% (41). However, a screening in 2019 of all adult residents of Rapa, the most isolated island of the Austral archipelago, revealed a prevalence of HBsAg of 11% in people born before 1992 (20).

Among the CDs considered as important public health issues in French Polynesia, those caused by arthropod-borne viruses (arboviruses) represent the highest risk for the population. Indeed, the four serotypes of dengue virus (DENV-1 to −4) have caused multiple outbreaks over the last decades, with deaths frequently reported in children (42, 43). Moreover, Zika virus (ZIKV) and chikungunya virus (CHIKV) caused explosive outbreaks in 2013–2014 (44) and 2014–2015 (45), respectively. During the ZIKV outbreak, severe neurologic complications in adults (46) and central nervous system malformations in newborns and fetuses (47) were recorded. In addition to arboviral diseases, CDs caused by respiratory viruses have become major health concerns over the past decades. Several epidemics of variable severity caused by influenza A and/or B viruses have been reported in French Polynesia (29). While influenza was not considered a public health priority until the early 2000s, an epidemic caused by the influenza A virus subtype H1N1 highly affected the population of French Polynesia in 2009, with 13 severe cases requiring hospitalization in a critical care service and 7 recorded deaths (48). More recently, the severe acute respiratory syndrome coronavirus 2 (SARS-CoV-2) reached French Polynesia in March 2020 and caused several epidemic waves, with a total of 78,864 confirmed cases, 3,315 hospitalizations and 783 deaths reported as of August 31, 2022. A serosurvey conducted at the end of 2021, from a representative sample of the adult population of Tahiti, found that 57.7% of the study participants had been infected by SARS-CoV-2 during the first two epidemic waves (49).

Bacterial infections also represent a significant risk for the population of French Polynesia. The incidence of leptospirosis, a rodent-borne disease caused by bacteria belonging to the order *Spirochaetales*, exploded in 2017 with a rate of 72/100,000 inhabitants (50). Moreover, the incidence of *Staphylococcus aureus* (*S. aureus*) infections was estimated at 38/100,000 inhabitants in 2008, and this bacterium was shown to be responsible for one third of the community bacterial infections documented in French Polynesia. The proportion of *S. aureus* strains resistant to methicillin increased from less than 10% in 1995 to more than 35% in 2001 (51). French Polynesia is also characterized by the unusual high prevalence of acute rheumatic fever associated with infection by Group A streptococcus, with an incidence of 0.06% and a prevalence of 1.29% reported in 2015 (29, 52).

Although data exist on the levels of exposure of the population and the risk factors associated with NCDs and CDs in French Polynesia, these data are often old, fragmentary and concern a few islands. Moreover, genomic data, based on whole genomes, from the Polynesian populations are lacking, precluding a comprehensive assessment of the settlement history of the various islands and archipelagoes, and of the history of genetic adaptation of these populations to island environments—an information that should be of great benefit for the study of the genetic basis of certain diseases that present high incidence in the region. Here we describe the MATAEA project, a wide cross-sectional population-based survey designed to investigate the determinants of health in the adult population of French Polynesia, using a combination of data obtained from a questionnaire, physical measurements, and biological analyses in 2,100 inhabitants of 18 different islands distributed among the five archipelagoes.

## Study objectives

MATAEA is a Tahitian compound word (“MATA” means “eye” and “EA” means “health”) which can be translated as “take a look at health”. The first objective of the MATAEA project was to collect a wide range of data from a large number of inhabitants to assess the health status of the adult population of the five French Polynesian archipelagoes, and identify risk factors for NCDs and CDs related to the specific living context (including the lifestyle, place of residence, history of infections) and intrinsic characteristics of individuals (such as genetics, age, sex, oral and gut microbiome). Results will be made available to health authorities for them to adapt actions and preventive measures to better reduce disease incidence. The second objective of the project was to use genomic data obtained from the residents to increase our understanding of the history of the settlement of the French Polynesian islands, and to identify the major demographic and adaptive events that may explain the current incidence of some NCDs, and the higher susceptibility to certain NCDs and CDs. Although designed as a general-purpose survey with a broad scope, topics identified as major public health issues will be given priority treatment by specialized laboratories involved in the project, as described below.

First, prevalence data for metabolic diseases (including obesity and diabetes) dating from 2010 will be updated (14), and their associated risk factors (such as dietary habits, physical activity, blood pressure, high blood sugar, excess body fat around the waist, abnormal cholesterol or triglyceride level, genetic susceptibility factors, microbiome composition) will be investigated.

Second, the seroprevalence of mosquito-borne diseases known to have previously circulated in French Polynesia (including the four serotypes of dengue, Zika and chikungunya) will be measured as previously published (53, 54), to assess the risk for new outbreaks to occur. In addition, the prevalence of filarial antigenemia will be evaluated to check whether the elimination threshold recommended by the WHO has been reached in all archipelagoes, subsequent to the strengthening of community treatment in islands most affected by Bancroftian lymphatic filariasis (37). Risk factors for those mosquito-borne diseases will also be sought. Among them, the level of exposure of the population to mosquito bites will be measured by analyzing the presence of IgG antibodies targeting mosquito salivary proteins in the blood of participants, as previously described (55).

Third, screening for HBsAg and anti-HBV total antibodies will be performed to assess the prevalence of current and past HBV infections among the inhabitants of the five archipelagoes, especially those with increased risk factors, such as being born before 1995 and living in the Austral archipelago. As there is no available data regarding the prevalence of hepatitis C virus (HCV) infections in French Polynesia, the presence of anti-HCV IgG antibodies will also be tested.

Fourth, concentrations of several heavy metals (including mercury and lead) and pesticides will be measured in the blood of inhabitants of the five archipelagoes to assess the degree of environmental contamination and the risk for human health. Data collected in the questionnaire, such as the island of residence and dietary habits, will be used to identify risk factors associated with contamination with toxic metals and pesticides, as well as ciguatera poisoning. As there is no confirmatory test available to detect current or past ciguatera poisoning, the estimate of the prevalence of this disease in the population of the five archipelagoes will be based on the information self-reported by the participants in the questionnaire.

Fifth, as SARS-CoV-2 was introduced into French Polynesia during the participants' inclusion period and a large number of cases with mild or no symptoms might have not been reported, the presence of specific IgG antibodies will be analyzed in the blood samples of participants to evaluate the real proportion of the population infected in the different archipelagoes after the emergence of the virus.

Sixth, serological analysis will be conducted for a panel of viruses known to regularly cause infections in French Polynesia (such as influenza viruses, human immunodeficiency virus, rotaviruses and enteroviruses), but for which there is little data on the immune status of the population.

Finally, the seroprevalence of rodent-borne pathogens including Hantaviruses will be determined, as the high incidence of leptospirosis suggests that other diseases transmitted by rodents may circulate in French Polynesia. The only serosurvey of hantavirus infections in French Polynesia was conducted in 1989 and found specific antibodies in a few samples from rats and humans (56). Consequently, data collected in the present study will allow detection of possible silent circulation of Hantaviruses.

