## Materials and methods

### Sampling design

The MATAEA project is a cross-sectional population-based survey conducted on a random sample of the general population aged from 18 to 69 years, representative of the five archipelagoes of French Polynesia. The sampling protocol is based on the previous population census dating from 2017 (1). A sample with a target size of 2,100 participants, equally divided into three age groups (18–29, 30–44 and 45–69), with a sex ratio of 1:1, was established. The sample size was determined using the following formula: *n = z² p (1-p)/d²*, where *z* is the level of confidence set at 95% (*z* = 1.96), *p* is the expected prevalence set conservatively at 50%, and *d* is the precision set at 3.7%. To represent all archipelagoes, French Polynesia was stratified into three geographical strata: Windward Islands (Society archipelago), Leeward Islands (Society archipelago), and other archipelagoes (Tuamotu, Gambier, Marquesas and Austral), which respectively include 75%, 13% and 12% of the population (Table 1). Since the population size in the Windward Islands is much higher than in the Leeward Islands and in the other archipelagoes, the sample size was amplified in the latter two strata to keep sufficient precision around prevalence estimates for the health conditions under consideration. Consequently, the same sample size of 700 subjects was chosen for the three strata, allowing a precision never exceeding +/− 3.7% around prevalence estimates within each stratum. In each stratum, for convenient reasons, the most populated islands with a health care center and an airport with regular flight rotations were selected for the study, and the number of participants to be recruited was proportional to the population size of the islands as detailed in Table 1. In each island, households were randomly selected by the *Institut de la Statistique de la Polynésie française* (ISPF, Tahiti), and in each household one resident meeting the criteria of age and sex sought for the study was recruited.

**Table 1 T1:** Geographical distribution of the 2,100 participants randomly selected for the MATAEA project.

Strata			Archipelago	Island		
Name	Population size (%)^a^	Sample size	Name	Name	Population size (%)^a^	Sample size
Windward Islands	207,333 (75%)	700	Society	Tahiti	189,517 (91%)	637
				Moorea	17,816 (9%)	63
Leeward Islands	35,393 (13%)	700	Society	Raiatea	12,249 (36%)	252
				Bora Bora	10,549 (31%)	217
				Tahaa	5,234 (15%)	105

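### The filariasis threshold is checked by archipelago, although the 2013 failures are reported by island, two of those five islands are not sampled, and a pooled figure can hide the others

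*Protocol article*

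**What the plan says.** Under Study objectives, second topic, the plan states that "the prevalence of filarial antigenemia will be evaluated to check whether the elimination threshold recommended by the WHO has been reached in all archipelagoes". The same sentence places this check "subsequent to the strengthening of community treatment in islands most affected by Bancroftian lymphatic filariasis".

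The Introduction gives the threshold as antigenemia below 1% and lists where it had not been met in 2013: Tahiti, Huahine and "three islands in the Marquesas archipelago (Tahuata, Hiva Oa and Fatu Hiva), despite several years of community treatment".

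Under Sampling design, islands were chosen for convenience: "the most populated islands with a health care center and an airport with regular flight rotations were selected for the study". Table 1 then lists three Marquesas islands: Nuku Hiva (91 participants), Hiva Oa (70) and Ua Pou (63). It also lists Tahiti (637) and Huahine (126). Tahuata and Fatu Hiva do not appear.

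Under Data analysis, prevalence is weighted by the inverse of the sampling probability.

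**The concern.** The evidence that motivates the check is by island, and so is the strengthened treatment. The check itself is worded by archipelago. Two things follow. Islands without participants cannot influence the result at any prevalence. Sampled islands with a small population share are diluted by their neighbours.

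The article intends the results to guide health authorities in adapting preventive measures. A Marquesas or Leeward figure below 1% could be read as the threshold having been reached while a named island is still above it or was never observed. A larger sample on the same 18 islands would not change that.

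**Working it through.** **The plan's own figure.** The sample size formula with z = 1.96, p = 0.50 and d = 0.037 gives n = 1.96² × 0.25 / 0.037² = 701.5, against 700 stated per stratum. The figure reproduces. It concerns precision at 50% prevalence in a stratum and does not address a 1% threshold on an island.

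**Inputs (Table 1).** Census populations: Nuku Hiva 2,951; Hiva Oa 2,243; Ua Pou 2,213; Raiatea 12,249; Bora Bora 10,549; Tahaa 5,234; Huahine 6,075; Tahiti 189,517; Moorea 17,816. The documents give no current prevalences, so those below are assumptions. Shares use total population, which assumes similar proportions of adults aged 18–69 across islands.

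**Coverage of the named islands.** Marquesas participants: 91 + 70 + 63 = 224. Of these, 91 + 63 = 154 (69%) are on islands not on the 2013 list. Tahuata and Fatu Hiva: 0.

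**Break-even formula.** If an island has population share w and the rest average r, the pooled figure reaches 1% when the island is at (1% − (1 − w) × r) / w.

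- Marquesas, Hiva Oa: w = 2,243 / 7,407 = 0.303. With r = 0%: 1% / 0.303 = 3.3%. With r = 0.5%: (1% − 0.697 × 0.5%) / 0.303 = 2.2%.
- Leeward stratum, Huahine: w = 6,075 / 34,107 = 0.178. With r = 0%: 1% / 0.178 = 5.6%. With r = 0.5%: (1% − 0.822 × 0.5%) / 0.178 = 3.3%.
- Society as a whole, Huahine: w = 6,075 / 241,440 = 0.0252, and Tahiti's share is 189,517 / 241,440 = 0.785. The result therefore depends on Tahiti. With Tahiti at 1% and the rest at 0%: (1% − 0.785%) / 0.0252 = about 8.5%. With Tahiti at 1% / 0.785 = 1.27%, Society is at 1% whatever Huahine shows.

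**Chance of a masked result (simple binomial sampling).** Suppose Huahine is truly at 3%. The observed Leeward figure is below 1% (at most 6 positives of 700) with probability 0.91 if the other islands are at 0%, and 0.50 if they are at 0.5%. Huahine's own observed figure would be above 1% (at least 2 of 126) with probability 0.895. At a true 5% that probability is 0.988.

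**What island figures can show.** With zero positives the two-sided exact 95% upper bound is 1 − 0.025^(1/n), with no design effect:

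| Island | n | Upper bound |
|---|---|---|
| Tahiti | 637 | 0.58% |
| Huahine | 126 | 2.89% |
| Hiva Oa | 70 | 5.13% |
| Tahuata, Fatu Hiva | 0 | no estimate |

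An upper bound below 1% needs ln(0.025) / ln(0.99), that is 368 all-negative participants. Of the five named islands, only Tahiti has that many.

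**The case against.** The strongest reply is that the reference to all archipelagoes may only describe geographic scope. The sentence names no pooled estimator and no decision rule, and island tables are not excluded; a full protocol or SAP may contain them. The limitations section also says that only 18 of 75 inhabited islands were sampled and that islands within an archipelago may differ. This stands in part: nothing in the article says that elimination will be declared from an average, and a reader should not infer that it will. But the stated unit is still the archipelago, and the general limitation neither mentions that two of the five named islands are unobserved nor restricts the elimination conclusion. Island tables could not supply data for those two.

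Three stronger readings are tempting and are not supported:

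- A reader might compute that Huahine could reach about 40% (1% / 0.0252) before Society reads 1%. That needs Tahiti at 0%, although Tahiti is itself on the 2013 list and carries 78% of the weight.
- A reader might infer that an archipelago can be below 1% with every named island in it above 1%. For Society this works only if Tahiti lies between 1.00% and (1% − 0.0252 × 1%) / 0.785 = about 1.24%, with Huahine little above 1% at the upper end and the other islands at zero.
- A reader might take the infection to be confined to the five islands. The Introduction says only that these had not met the threshold; it does not say that the others were tested and clear.

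It is also fair to object that the island samples are too small to replace the check. They are, for confirming elimination. They can still reveal persistence.

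**Conclusion.** The point holds. As worded, the check can return a figure below 1% for the Marquesas or the Leeward stratum while a named island remains above 1%, and it can say nothing about Tahuata or Fatu Hiva. The masking range is up to about 3.3% to 2.2% on Hiva Oa, with 0% to 0.5% on the other two sampled Marquesas islands, and up to about 5.6% on Huahine within the Leeward stratum with 0% elsewhere. Society-wide, the dilution of Huahine cannot be stated without a value for Tahiti; it is about 8.5% if Tahiti is at 1%. All of these rest on assumed prevalences and Table 1 population shares. They show what a pooled figure could hide, and are no evidence that any island is above the threshold now.

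**What to change.** - Limit the filariasis objective to the sampled islands.
- Report antigenemia separately for Tahiti, Huahine and Hiva Oa with exact intervals, alongside the archipelago or stratum estimates.
- Do not report the threshold as reached for an archipelago in which a named island is above 1% or was not sampled.
- State that no elimination conclusion applies to Tahuata, Fatu Hiva or the Marquesas as a whole.

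Recruitment ended in December 2021, so this is a change to wording and reporting: a reworded objective and one more table from data already planned. The price is a narrower and less favourable conclusion. Huahine and Hiva Oa can show that infection persists, but their samples cannot confirm elimination; of the named islands only Tahiti could be shown to be below 1%.
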